### Trial design {8}

The study consists of a single-arm phase I part and a randomized, parallel-group, and unblinded phase II part.

In phase I, patients with the first relapse of MGMT-methylated glioblastoma are screened for the trial. After inclusion, patients are pretreated with MFA in addition to standard TMZ and tumor resection will be performed 7–10 days after initiation of therapy. MFA tissue level measurements and translational analyses are performed on the tumor material obtained from resection. Each patient is particularly screened for dose-limiting toxicities (DLTs) during the first 8 weeks of his/her MFA treatment. Patients are recruited in two cohorts of three to six patients. Dose adaptation in between cohorts depends on the occurrence of DLTs as described below.

All patients of phase I are followed for toxicity and efficacy until the end of phase II.

In phase II, patients with the first relapse of MGMT-methylated glioblastoma are screened for the trial. After inclusion, patients are randomized (1:1) into two parallel groups, the experimental or the standard treatment arm. The experimental treatment is defined as treatment with MFA (dose determined in phase I) in addition to standard TMZ. The standard treatment arm is defined as monotherapy with TMZ (150–200 mg/m^2^ body surface). If tumor resection for the relapsed tumor is clinically indicated, the local treating neurosurgeon can decide whether the resection can be safely postponed until day 7–10 after initiation of therapy (optional, not a prerequisite for study participation in phase II) and tumor material for determination of MFA levels can be obtained.

MFA is taken at the dose determined in phase I. Daily MFA treatment is continued for 8 4-week courses (i.e., 224 days), until tumor progression, until the occurrence of a DLT attributable to MFA, or until definitive discontinuation of standard TMZ, whatever comes first. In case MFA therapy is terminated, standard TMZ therapy can be continued at the discretion of the treating physician.

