### Outcomes {12}

In phase I, the primary outcome to be evaluated will be the incidence of DLTs during the first 8 weeks of MFA treatment. DLT for each dose level is defined as any CTCAE5 grade 3/4 organ toxicity or grade 4 hematotoxicity > 2 weeks during the first 8 weeks of MFA treatment; events probably related to the tumor resection and/or perioperative treatment or to the underlying disease are not regarded as DLT. Secondary outcomes in phase I are progression-free survival (PFS) as measured from the inclusion into the trial until diagnosis of progressive disease determined by MRI (according to “response assessment for neurooncology” (RANO) criteria) in the local center, PFS according to post hoc central reference neuroradiological assessment, overall survival (OS) as measured from the day of inclusion into the trial, assessment of safety beyond 8-week MFA treatment, and Karnofsky Performance Score (KPS), Quality of life (QoL), and Mini-Mental State Examination (MMSE) throughout the trial.

In phase II, the primary outcome to be evaluated will be PFS (randomization until the diagnosis of progressive disease according to RANO criteria). Secondary outcomes will be OS (randomization until death), continuous monitoring of AE/severe adverse events (SAE)/suspected unexpected serious adverse reactions (SUSARs), and quality of life throughout the trial (measured by KPS, QoLs, and MMSE). Survival analyses also include patients from phase I who received MFA at the same dose as applied in phase II.

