**Table 1 Tab1:**
[figure not shown]
Visits and assessments in the MecMeth/NOA-24 trial

*DLT visit will only be performed in phase I. In phase I, visit 2.3 is only performed additionally; if the start of cycle 3 is prolonged for more than 3 days after the DLT visit, all patients in phase II have visit 2.3

**EoT: end of treatment is reached 3 days after last MFA intake (phase I and experimental arm of phase II) or on day 31 of the last TMZ cycle (standard arm of phase II)

***End of study and of follow-up in the entire trial will be reached when *both* of the following requirements are fulfilled: (1) at least 6 months after randomization of the last patient in phase II *and* (2) at least 3 days after definite termination of MFA intake in the last patient receiving MFA therapy (i.e., all patients have concluded study-related MFA intake for more than 3 days)

^1^Every 8 weeks: progression assessment, Karnofsky score and QoL, blood samples

^2^Na, K, creatinine, ASAT, ALAT, bilirubin

^3^Gadolinium-enhanced MRI obtained prior to inclusion/randomization can be used as baseline MRI if the interval between this MRI and the start of study therapy is shorter than 21 days. In patients who have undergone re-resection prior to randomization (only possible in phase II), the MRI used as baseline MRI has to be a postoperative MRI

^4^Relapse tumor resection 7–10 days after initiation of study therapy, tissue asservation should take place 2–4 h after the last intake of MFA/TMZ: (1) fresh frozen, (2) 4% PFA, and (3) FFPE tumor material for MFA/MFA metabolite level determination and for analysis of MFA-dependent tissue effects. The exact timepoint of the last MFA intake prior to resection and the exact timepoint of asservation of the tumor material have to be documented

^5^Timepoints (to be documented): (a) 2 h after first intake, (b) on the days between MFA start and resection daily blood sampling 2 h after morning application of MFA (optional), and (c) on the day of resection 5 blood samples at an interval of 2 h (0 h (prior to last preOP MFA dose) 2 h, 4 h, 6 h, 8 h later)

^6^Only at the first follow-up visit after discontinuation of MFA

^7^Only during ongoing MFA treatment + 3 days

^8^Only if clinically indicated

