Briefly, patients start therapy within 7 days after inclusion/baseline visit. If according to the local treating neurosurgeon and the local neurooncological tumor board, re-resection of the tumor is clinically indicated and can be safely deferred until day 7–10 after initiation of MFA/TMZ therapy, tumor resection is performed 7–10 days after initiation of therapy. This is mandatory in phase I and optional in phase II. Resected tumor tissue is used for translational analyses of intratumoral MFA/MFA metabolite levels and detection of cellular and molecular effects of MFA. Also, blood analyses are performed for the determination of MFA blood levels 2 h after the first intake of MFA on day 1 and at 5 timepoints on the day of resection. During therapy, further visits are scheduled every 4 weeks prior to the start of a new TMZ cycle. These visits include clinical and standard laboratory examinations, documentation of co-medication documentation of (S)AE, KPS, and, every 8 weeks, contrast-enhanced MRI and QoL evaluation. In phase I, DLT evaluation is added at the visits prior to cycle 2 (day 28 ± 3) and cycle 3 (day 56 ± 3). MFA/TMZ treatment ends after 8 4-week cycles, at progression, or if MFA or at the timepoint when MFA or TMZ treatment has to be prematurely discontinued for whatever reason, e.g., intolerable toxicity, whatever comes first. After the end of the study therapy, patients are followed with clinical examination, contrast-enhanced MRI, and documentation of KPS, QoL, and further tumor therapy every 8 weeks. End of study and of follow-up in the entire trial will be reached when both of the following requirements are fulfilled: (1) at least 6 months after randomization of the last patient in phase II and (2) at least 3 days after definite termination of MFA intake in the last patient receiving MFA therapy (i.e., all patients have concluded study-related MFA intake for more than 3 days).

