### Methods in analysis to handle protocol non-adherence and any statistical methods to handle missing data {20c}

In phase I, patients who are not evaluable for DLT will be replaced. A patient is evaluable for DLT if the DMSB has determined that a DLT has occurred in this patient during the first 56 days after treatment start (independent of the duration of MFA intake) or if until DLT visit (day 56 ± 3 days after start of MFA treatment) the patient has taken at least 100 doses of MFA (i.e., 89.3% of the maximally positive cumulative dose in 56 days) as documented by the patient’s diary and the documented return of 1 empty container of MFA (containing 100 capsules) (for dose step 2 × 100 mg daily or 2 × 50 mg daily) or of 2 empty containers of MFA (for dose step 2 × 200 mg daily).

In phase II, subjects dropping out of the trial prior to randomization will be listed as screening failures including the reason for dropout. Subjects prematurely discontinuing the trial will be censored regarding the analysis of PFS or OS at the time of discontinuation. Subjects dropping out after randomization will be analyzed using all available data and will not be replaced. The technique for the analysis of missing values will be defined in the statistical analysis plan. A check of a possible treatment effect on the frequency of missing values will be performed.

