### Adverse event reporting and harms {22}

Any AE and SAE (per definition in the trial protocol) has to be documented in the CRF on the respective adverse event report form. AE/SAE documentation will be performed for each participant between the baseline visit and the visit at least 3 days after termination of MFA administration. AEs will be reported and evaluated according to the Common Terminology Criteria for Adverse Events (CTCAE5). According to the GCP-V, only AEs and unexpected clinical diagnostic findings that are identified in the protocol as critical for clinical trial evaluation must be documented and transmitted to the sponsor. To ensure comparability of the safety data of the two study arms, any adverse medical incident in patients of the control arm will also be recorded although no study drug will be administered. Whenever possible, diagnoses should be given when signs and symptoms are due to a common etiology. All measures required for adverse event management must be recorded in the source document and reported according to sponsor’s instructions. The investigator evaluates all AEs regarding severity, causality, and seriousness. Every SAE has to be reported immediately via fax to the Study Coordinating Center at the SZB. To take into account safety data available to the sponsor but not to the investigator at the time the SAE was detected, in addition to the initial assessment of a SAE by the investigator, a second assessment of the event by the sponsor in terms of causality and probability of occurrence (“expectedness”) and a continuous benefit-risk assessment are performed.

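### Phase I counts a DLT up to day 56 whatever the MFA duration, but adverse event recording is tied to the end of MFA, so late DLTs in early stoppers are not assured of being recorded

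*Protocol article*

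**What the plan says.** All references are to the protocol article.

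- **What counts.** Section {20c} counts a DLT "during the first 56 days after treatment start (independent of the duration of MFA intake". Section {11a} also dates the window from first study treatment, 56 (±3) days. Section {12} words the primary outcome as the "incidence of DLTs during the first 8 weeks of MFA treatment".
- **What is recorded.** Section {22} has AE/SAE documentation run "between the baseline visit and the visit at least 3 days after termination of MFA administration". A Table 1 footnote says that "end of treatment is reached 3 days after last MFA intake (phase I and experimental arm of phase II".
- **When patients are seen.** Section {13} describes four-weekly visits during therapy with laboratory tests and AE documentation, and adds the DLT evaluations on days 28 ± 3 and 56 ± 3 to these visits. It treats MFA/TMZ treatment as ended when either drug has to be stopped prematurely. After study therapy, "patients are followed with clinical examination, contrast-enhanced MRI, and documentation of KPS, QoL, and further tumor therapy every 8 weeks".
- **Contrary statements.** Section {8}: "All patients of phase I are followed for toxicity and efficacy until the end of phase II". Section {18b} asks patients who stop MFA to remain in follow-up, with AE data named among the items to be obtained.
- **Evaluability.** Without a DLT, a patient is evaluable only if by the DLT visit "the patient has taken at least 100 doses of MFA (i.e., 89.3% of the maximally positive cumulative dose in 56 days". Section {20c} also states: "In phase I, patients who are not evaluable for DLT will be replaced".

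**The concern.** The period over which a DLT counts and the period over which adverse events must be recorded have different end points. The first is fixed at day 56; the second moves with the last MFA dose. They agree for a patient who takes MFA throughout the window and separate for one who stops early, often for poor tolerance, in whom delayed toxicity is of most interest.

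Hematological DLTs are the most exposed. Section {11a} requires grade 4 or higher toxicity lasting more than 14 days, and such an episode beginning after the stop cannot have its duration established in a tail of about 3 days. Suppose a patient stops MFA on day 20 for toxicity below DLT grade and has grade 4 thrombocytopenia from day 26 to day 44. If judged MFA-related, this is a DLT under section {20c}. A site working from section {22} could have closed AE documentation around day 23.

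That patient has too few doses to be evaluable and would be replaced, so the event leaves the count that sets the phase II dose.

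**Working it through.** **The plan's own figure.** The maximum is 2 × 56 = 112 doses, and 100/112 = 89.3%, as section {20c} states. At two doses a day, 100 doses is 50 days, and 50/56 is also 89.3%; section {11a} rounds this to 90%. A patient without a recorded DLT who stops before day 50 is therefore not evaluable and is replaced.

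**Length of the gap.** On a literal reading of section {22}, with the closing visit 3 days after the last dose on day d, the uncovered part of the window is 56 − (d + 3) days:

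| Last MFA dose (day d) | AE documentation to day | Days uncovered | Share of 56 |
|---|---|---|---|
| 14 | 17 | 39 | 69.6% |
| 28 | 31 | 25 | 44.6% |
| 42 | 45 | 11 | 19.6% |
| 50 | 53 | 3 | 5.4% |

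**Next scheduled contact.** If the 8-weekly follow-up is counted from the end-of-treatment visit, the first one falls on day d + 3 + 56 = d + 59: day 73 for d = 14 and day 87 for d = 28, always after the window. If it is counted from treatment start, it coincides with day 56. The text does not say which applies.

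**Effect on the dose decision.** Under section {11a}, a dose level passes with 0/3 DLTs, or with 1/3 followed by 0/3. With DLT probability p,

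P(pass) = (1 − p)³ + 3p(1 − p)⁵.

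If a share f of DLT patients is missed and replaced, the DLT rate among patients who remain evaluable is

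p′ = p(1 − f) / (1 − pf).

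Both p = 1/3 and the values of f are assumptions; the document gives neither.

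| f | p′ | P(pass) |
|---|---|---|
| 0 | 0.333 | 0.296 + 0.132 = 0.43 |
| 0.10 | 0.300/0.967 = 0.310 | 0.328 + 0.145 = 0.47 |
| 0.25 | 0.250/0.917 = 0.273 | 0.385 + 0.166 = 0.55 |
| 0.50 | 0.167/0.833 = 0.200 | 0.512 + 0.197 = 0.71 |

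**Plausibility of f.** Section {14} allows 1/6 of patients for replacement for any reason, including missing tumor levels. At p = 1/3, f = 0.25 means that 1/3 × 0.25 = 1/12 of all patients have a missed DLT, half of that allowance. With f = 0.50 the share is 1/6, the whole of it. The last row is therefore an outer bound on the plan's own expectation.

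**The case against.** The strongest reply is that follow-up after an MFA stop is prescribed. Section {8} follows all phase I patients for toxicity to the end of phase II. Section {18b} seeks AE data after MFA stops, requires clinical and MRI follow-up after any discontinuation, and follows significant abnormalities still present at withdrawal until they resolve or stabilize. No visible text cancels the day-56 DLT visit, which section {20c} dates from the start of MFA, and Table 1 itself is not shown. Section {22} sets a minimum of 3 days, not a cut-off, and a Table 1 footnote lists blood samples every 8 weeks. In addition, MFA-related grade 3 or higher organ toxicity that stops treatment is in most cases already a DLT and would be recorded at that point.

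Much of this stands. A reader might infer that early stoppers go wholly unobserved for the rest of the window. The document does not support that, and the gap lengths above are a literal worst case.

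Two further inferences also fail. One is that a single missed DLT simply turns a blocking 2/6 into a clearing 1/6. The other is that missing a quarter of DLTs raises clearance to 0.60, which follows from putting p = 0.25 into the formula. Both treat the missed patient as DLT-free, whereas section {20c} replaces that patient with one who may also have a DLT.

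The reply does not remove the contradiction. Follow-up to resolution covers only what is present at withdrawal, not what arises later. Follow-up under section {18b} is according to the protocol, which leads back to the section {13} list. Sections {8} and {18b} state an intention without an AE schedule, while section {22} gives sites an operational window that ends sooner.

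**Conclusion.** The point holds as an internal contradiction: sections {22} and {13} and the Table 1 end-of-treatment footnote against sections {8}, {18b} and {20c}. For a phase I patient who stops MFA early without a DLT, recording of a later DLT up to day 56 is not assured. The literal gap is 39 days for a stop on day 14 and 25 days for day 28.

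Replacement limits the damage but does not remove it. Any DLT missed this way leaves the count, so the bias runs toward clearing the dose. Its size is unknown. At an assumed true rate of 1/3, clearance rises from 0.43 to about 0.47, 0.55 or 0.71 if 10%, 25% or 50% of DLT patients are missed and replaced. The direction does not depend on those assumptions. Because the phase II dose rests on very few patients, the windows should be aligned. The point concerns the phase I primary outcome only, not the randomized comparison.

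**What to change.** In section {22}, with matching wording in section {13} and the Table 1 footnotes, state that for every phase I patient who took any MFA, AE/SAE and laboratory documentation and the day-28 and day-56 DLT evaluations continue to the later of day 56 and 3 days after the last MFA dose.

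Word the window in section {12} as in sections {11a} and {20c}: 56 days from first study treatment, independent of MFA duration. The 90% compliance condition in section {11a} should then carry the exception that section {20c} already makes for patients with a DLT. Reconcile all of these with sections {8} and {18b}.

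This changes observation only, not treatment. It costs protocol wording and one or two already defined visits in the few phase I patients who stop MFA early.

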### Sample size {14}

Phase I uses an adaptive design based on DLTs (see Fig. 1). Starting with 3(-6) patients per dose level is standard for dose finding in phase I. Starting with a middle-level MFA dose of 2 × 100 mg/day (according to the US registration of MFA) ensures that only two dose levels have to be explored (*n* = 6–12 patients). Patients not evaluable for DLT or MFA tumor levels will be replaced (conservative estimate, 1/6 patients; thus maximal patient number in phase I, 12 + 2 = 14).

The randomized phase II part accrues 30 patients per arm. For the evaluation of PFS, the experimental arm also includes the 3–6 patients of phase I which have been treated with the same dose of MFA as in phase II for an additional analysis. Since phase II is searching for indications of efficacy but is not a confirmatory trial, dropouts will not be replaced. In glioblastoma trials, the dropout rate is relatively low (e.g., 9% in CeTeG/NOA-09 trial). Therefore, and since data from dropout patients are included as censored observation, the results may be expected to be robust regarding patients with short follow-up/early dropouts.

With 30 subjects per arm and a two-sided alpha level of 10%, we could detect a hazard ratio of approximately 0.44 if we assume a PFS-6 of 40% for the reference treatment and use a power of 80%.

### Recruitment {15}

Adequate participant enrolment will be achieved by continuous screening for potential participants in all participating centers. This is achieved by discussing every patient with a relapsed glioblastoma who is seen at a participating site in the interdisciplinary neurooncological tumor board which is mandated by German certification rules. This allows that all potentially eligible patients in a center can be identified.

## Assignment of interventions: allocation

### Sequence generation {16a}

The allocation to the treatment group in the phase II part will be performed electronically via the validated randomization tool of the electronic case report form (CRF) systemMARVIN (XClinical). The randomization will be performed using permuted blocks with a variable block size.

### Concealment mechanism {16b}

The usage of the electronic randomization tool in the electronic case report form (CRF) system described above ensures that the sequence is concealed until the intervention is assigned.

### Implementation {16c}

The allocation sequence is generated randomly by the computer-based MARVIN randomization tool implemented by the statistician of the Clinical Study Core Unit Bonn (SZB). After input of all data necessary for randomization (inclusion/exclusion criteria, demographic data), the electronic system displays the randomization result.

## Assignment of interventions: blinding

### Who will be blinded {17a}

In phases I and II, neither trial participants nor care providers will be blinded. However, neuroradiologists performing a post hoc re-analysis of the MRIs will be blinded for treatment protocol.

### Procedure for unblinding if needed {17b}

Unblinding will not be needed.

## Data collection and management

### Plans for assessment and collection of outcomes {18a}

Assessment and collection of baseline, outcome, and other trial data will be performed by the local investigator in the study visits and by evaluation of MRI scans by neuroradiologists. Every delegated assessor will be trained by a qualified trainer. The following study instruments will be utilized: questionnaires, laboratory tests, MRI scans, MMSE, (optional) electro-encephalography (EEG), or magnetic encephalography (MEG). A summary of the data to be collected is given in Table 1. Case report forms (CRFs) will be provided at the homepage of the clinical neurooncology division of the University of Bonn.

### Plans to promote participant retention and complete follow-up {18b}

To promote participant retention and complete follow-up, patients will be closely monitored. Besides, they will always have the chance to contact a responsible person at the site. Contact data (telephone numbers, email) will be given to the patient at the beginning of the trial. If participants decide to discontinue MFA treatment, they will be asked to stay in the follow-up for their own safety and to obtain follow-up data (AE, PFS, OS). If they are not willing to do so, the investigator is urged to ask the subject to return for an early termination visit and to document subject outcome (AE, PFS, OS), if possible. Any clinically significant abnormalities persisting at withdrawal will be followed by the investigator until resolution or until reaching a clinically stable endpoint. If a subject does not return for a scheduled visit, every effort will be made to contact the subject.

Subjects may also be withdrawn at any time at the discretion of the investigator for safety, behavioral, or administrative reasons. All patients who are discontinued from study therapy for any reason have to be followed according to the study protocol with clinical and MRI investigations until the end of the follow-up time of the whole trial (including the collection of all outcome data as described above).

